#### 2.4.3 Background descriptive measures.

The inclusion of confounders described in this section are based on previous literature [1,18,26,27]. Socio-economic status (SES), and gender will be used in all analyses. Age will be used in analyses related to FL and CCL. Food and cooking class participation will be included in analyses related to FL. Other covariates, such as related school activities, transport, weather, and the size of the school garden will be included in analyses relevant to PA.

***Socio-economic status (SES):*** When providing informed consent on behalf of their child(ren), information on parental educational background and occupation will be collected. Parents’ or guardians’ social class will be categorized using the Danish Occupational Social Class coding-scheme [55], which categorizes social class from one (highest) to six (lowest) based on, first, occupation, and, in case the occupation is not provided, educational background. The pupils’ SES will then be based on the parent or guardian with the highest social class in the case of joint custody. In the case of full custody, the pupils’ SES will be based on the social class of only this parent or guardian.

***Gender and age:*** Information on the pupils’ gender identification and date of birth will be collected electronically from the parent or guardian concurrent with the provision of informed consent. Gender will be collected by asking whether the pupil identifies as ‘girl’, ‘boy’ or ‘other’ and is subsequently used categorically. Age will be calculated in years from the date of birth using first of March 2024 as an endpoint and included as a continuous variable in the analyses.

***Related school activities:*** Teachers responsible for the participation of each school class will be asked to provide class-level information on the pupils’ school schedules. The information will be used assess whether the involved classes’ participate in food and cooking class (also referred to as food science or home economics in other countries) as part of their school curriculum during fourth grade or the first semester of fifth grade (binary variable: yes/no).

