### 2.1 The Gardens to Bellies program

The Danish school garden program GtB will serve as an intervention in this study (see the FoodACT study Logic Model, Fig 4). The GtB program is an ongoing educational initiative launched in 2006. School classes are invited to attend eight sessions (whole school days) in the school gardens (ten sessions/days in a few select municipalities) over the course of the second semester of fourth grade and the first semester of fifth grade (pupils approx. ten years of age, range nine to twelve). The school garden sessions start each year in March and end in October. Before the first school garden visit, an introductory workshop of one to two hours is conducted at the schools to spike the pupils’ curiosity. The school gardens are currently located in nine municipalities across Denmark. All participating school classes attend a school garden located in their own or near their own municipality, hence, the distance to the school garden as well as their mode of transportation to and from the school garden may vary across the participating schools. Furthermore, the plot size of the gardens varies across the garden locations.

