### 2.4 Sub-study 1: Effects of GtB on food literacy, climate change literacy, and school motivation

#### 2.4.1 Design.

SS1 will be designed as a clustered quasi-experimental study. The pupils’ FL, CCL, and SM will be measured with online questionnaires pre- and post-program in both the intervention and control group. The completion of questionnaires will be facilitated by the teacher responsible for the class’s participation in the study without the presence of the research team. Baseline data collection will commence one week prior to the start of the GtB program in the intervention group and within a matched two-week timeframe for the control group. Follow-up data collection will commence one week after the end of the GtB program in the intervention group, and accordingly, within a matched two-week timeframe for the control group. All questionnaires are in Danish and will be administered during school hours on computers with brief videos introducing each questionnaire.

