#### 2.4.5 Statistical analyses.

Linear mixed models will be applied to assess the intervention effects on FL, CCL, and SM [58]. Two-tailed tests with p-values below 0.05 will be considered statistically significant.

The analyses will account for the pupils’ nesting in their school classes by introducing school class as a random effect in the models. Intervention effects will be estimated through the inclusion of a group variable (intervention or control) and by adjusting for the outcome measure at baseline as well as confounders. Significantly better developments in these measures in the intervention group compared to the control group when adjusting for baseline level and confounders will be interpreted as a positive effect of the GtB program. Due to the lack of randomization, the analyses will be adjusted for known confounders such as gender, and SES. The analysis on the effect of GtB on FL will be further adjusted for participation in food and cooking classes during fourth grade or first semester of fifth grade. The analyses on the effect of GtB on FL and CCL will also be adjusted for age. Lastly, ICCs will be calculated by running the linear mixed models without the covariates to assess potential variation among school classes as fractions of the total variance. All analyses will be conducted using RStudio (version 1.4.1106; RStudio, Inc.) and IBM SPSS Statistics (version 29.0.1.0; IBM Corp.).

The models are expressed as follows:

$$\begin{array}{l} \text{Effect of GtB on FL:Endline FL }(\text{Y})=({\text{β}}_{0}+{\text{b}}_{\text{class}})+{\text{β}}_{1}\text{ FL baseline}+{\text{β}}_{2}*\text{int\_con}+{\text{β}}_{3}*\text{gender}+\\ {\text{β}}_{4}*\text{SES}+{\text{β}}_{5}*\text{age}+{\text{β}}_{6}\text{ food\_cooking\_class}+\text{ε} \end{array}$$

$$\begin{array}{l} \text{Effect of GtB on CCL:Endline CCL }(\text{Y})=({\text{β}}_{0}+{\text{b}}_{\text{class}})+{\text{β}}_{1}\text{ CCL baseline}+{\text{β}}_{2}*\text{int\_con}+\\ {\text{β}}_{3}*\text{gender}+{\text{β}}_{4}*\text{SES}+{\text{β}}_{5}*\text{age}+\text{ε} \end{array}$$

$$\begin{array}{l} \text{Effect of GtB on SM:Endline SM }(\text{Y})=({\text{β}}_{0}+{\text{b}}_{\text{class}})+{\text{β}}_{1}\text{ SM baseline}+{\text{β}}_{2}*\text{int\_con}+\\ {\text{β}}_{3}*\text{gender}+{\text{β}}_{4}*\text{SES}+\text{ε} \end{array}$$

Explanation for model concept for effects on FL, CCL and SM:

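### The cooking-class covariate in the food literacy model mixes teaching before baseline with teaching between the surveys, and can leave residual confounding if the timing mix differs between groups

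*Protocol article*

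**What the plan says.** Section 2.4.3 of the protocol article lists the covariates. Teachers "will be asked to provide class-level information on the pupils’ school schedules", and from this each class is classified by whether it has food and cooking lessons "as part of their school curriculum during fourth grade or the first semester of fifth grade (binary variable: yes/no"). The same section assigns the variable to one outcome: "Food and cooking class participation will be included in analyses related to FL".

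Section 2.4.5 repeats the window, saying that the FL analysis is "further adjusted for participation in food and cooking classes during fourth grade or first semester of fifth grade". The variable enters the FL equation as food_cooking_class with a single coefficient, alongside baseline FL, group, gender, SES and age, with a random intercept for class.

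The timing of programme and surveys is set elsewhere. Section 2.1 places the programme "over the course of the second semester of fourth grade and the first semester of fifth grade" and adds: "The school garden sessions start each year in March and end in October". Section 2.4.1 fixes the surveys: "Baseline data collection will commence one week prior to the start of the GtB program in the intervention group", and "Follow-up data collection will commence one week after the end of the GtB program in the intervention group". Controls are surveyed in matched two-week windows.

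**The concern.** The covariate window opens before the observation period. It includes the first semester of fourth grade and whatever part of the second semester precedes the baseline survey. Cooking teaching finished by then should show, at least in large part, in baseline FL, which the model already contains. Cooking teaching between the two surveys is different: it can move endline FL in parallel with the garden programme, and baseline FL cannot account for it. One yes/no flag gives both kinds of class the same code and the same coefficient.

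This matters because allocation is not randomised. Control classes come from other municipalities, chosen for similar average disposable income and proximity (section 2.2). Nothing in that selection balances when cooking is taught. If the groups differ in timing among classes coded yes, part of the difference in concurrent teaching stays in the group coefficient. Section 2.4.5 would read a significantly better adjusted development as a programme effect.

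**Working it through.** **1. Timing.** The sections side by side:

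| Period | In covariate window? | Between baseline and follow-up? |
|---|---|---|
| First semester of fourth grade | Yes | No |
| Second semester of fourth grade, before the baseline survey | Yes | No |
| Baseline survey to follow-up survey | Yes | Yes |
| First semester of fifth grade, after follow-up | Yes, if the semester runs that long (end dates not given) | No |

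Every class taught cooking during the programme is coded yes. The misclassified classes are those taught only outside the interval between the surveys.

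**2. The plan's own benchmark.** Section 2.4.4 gives 25 classes of 18 pupils per group, ICC 0.046, power 0.8, two-sided 0.05, three covariates and a minimum detectable effect of 0.255 (0.076 to 0.434). With 50 classes in all, equal split and 50 − 3 − 2 = 45 degrees of freedom:

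- SE = √[0.046/(0.25 × 50) + 0.954/(0.25 × 50 × 18)] = √(0.00368 + 0.00424) = 0.0890.
- Detectable effect = [t(0.975) + t(0.80)] × SE = 0.2549, interval 0.0756 to 0.4341.

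The stated figure is reproduced. At the recruitment target of 75 classes per group (section 2.2), with 18 pupils per class, the same formula gives SE 0.0514 and a detectable effect of about 2.82 × 0.0514 = 0.145.

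**3. Residual bias under the stated flag.** Let γ be the effect of concurrent cooking teaching on endline FL given baseline, in SD. Let q_I and q_C be the shares of yes classes taught during the programme in the intervention and control groups. Let p be the share coded yes, taken as equal in both groups, with equal group sizes. Suppose teaching before baseline adds nothing further once baseline FL is in the model. Among yes classes the groups then differ by γ(q_I − q_C); among no classes they differ by zero. The adjusted group coefficient averages these with weights p and 1 − p:

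bias = γ × (q_I − q_C) × p.

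The documents give none of γ, q_I, q_C or p. All are assumptions here.

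| γ | Timing difference | p | Size of bias (SD) | Share of 0.255 | Share of 0.145 |
|---|---|---|---|---|---|
| 0.2 | 20 points | 0.5 | 0.02 | 8% | 14% |
| 0.3 | 40 points | 0.5 | 0.06 | 24% | 41% |
| 0.2 | 20 points | about 1 | 0.04 | 16% | 28% |
| 0.3 | 40 points | about 1 | 0.12 | 47% | 83% |
| any | 0 | any | 0 | 0% | 0% |

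**4. Check by large-sample least squares on class types** (no cooking, before baseline only, during the programme):

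- p = 0.5, q 50% in intervention and 80% in control: bias −0.015, −0.038 and −0.060 SD for γ = 0.1, 0.255 and 0.4.
- p = 0.9, q 50% against 90%: −0.036, −0.092 and −0.144 SD.
- Groups swapped: the same sizes with the sign reversed.
- p = 0.5, q 70% in both groups: 0.000 throughout.
- Yes shares 30% against 60% with q 70% in both: unadjusted bias −0.054 SD at γ = 0.255, and 0.000 after adjustment for the stated flag.

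An indicator for teaching during the programme brought the bias to zero in every scenario.

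**The case against.** The strongest reply is that the variable does the job the protocol gives it. It is presented as a confounder, not as a measure of concurrent exposure alone, and its window contains the whole programme. The last scenario above shows that it fully removes bias from a difference in whether cooking is taught, provided the timing mix is alike. Cooking teaching before baseline is itself a legitimate confounder. Baseline FL may not absorb it completely, since the questionnaire was validated at ages 12 to 14 and modified for younger pupils. If earlier teaching keeps an effect δ beyond baseline, γ in the formula becomes γ − δ and the bias shrinks. All of this stands. It rules out a fix that drops teaching before baseline from the model.

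A reader might infer that the flag fails to measure the competing exposure, or that the model adjusts for the wrong thing. The documents do not support either reading: the exposure is measured, with misclassification. Nor do they support a claim that the FL effect is biased in a known direction, because they say nothing about the prevalence, timing or effect of cooking classes.

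A second reply is that teaching between the surveys is a post-baseline variable. Section 2.1 says teachers are encouraged to carry garden themes into the regular curriculum, so concurrent cooking lessons might partly follow from the programme, and adjusting for them could remove some of its effect. This is a fair caution, but the stated flag already includes the same teaching. It is not a reason to keep the two periods merged.

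**Conclusion.** The point holds as a coarse covariate definition in one model. The single flag cannot separate cooking teaching finished before baseline from cooking teaching between the surveys, and baseline FL cannot stand in for the latter. Residual confounding of the FL effect follows only if the timing mix among yes classes differs between groups. On the assumed inputs its size is 0.02 to 0.06 SD with half the classes coded yes, and up to 0.04 to 0.12 SD with nearly all coded yes. The upper figures should not be quoted without that condition. More classes reduce the standard error but not this bias, so it weighs more against the detectable effect at the recruitment target than against 0.255. The climate change literacy and school motivation models and sub-study 2 do not use this covariate, and no stated figure changes. The change is worth making because it is cheap, not because a bias has been shown.

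**What to change.** Ask teachers, with the class schedules already requested, for the semester or dates of food and cooking lessons. From these, code two class-level yes/no indicators:

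- cooking class before that class's baseline survey;
- cooking class between that class's baseline and follow-up surveys.

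Enter both in the FL model in place of food_cooking_class, and amend sections 2.4.3 and 2.4.5 to match. Keep the single flag, as now defined, as a sensitivity analysis. Tabulate both indicators by group, so that readers can see whether the timing mix differs.

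The cost is one line on the teacher form and one extra class-level parameter. The sample size does not change. When interpreting the result, note that the second indicator is measured after baseline and could be partly influenced by the programme, as the present flag could.

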#### 2.4.4 Sample size.

Based on the recruitment target of previous similar studies in a Danish school setting, power calculations were conducted using 25 school classes with an average of 18 pupils per class in each group to calculate a minimum detectable effect size. This approach was chosen due to the limited existing research on the effects of school gardens on the chosen outcomes of this study. Power calculations were completed in the R package PowerUpR. In the calculations, the clustered nature of data with pupils nested in classes was considered, conventional levels of statistical power (0.8), and 2-tailed level significance (0.05) were applied. An intraclass correlation (ICC) of 0.046 was used based on a similar dataset of pupils from a Danish study on EOtC [56]. Adjustments for three covariates were also included in the calculation. Power calculations show that with this sample, the minimum detectable effect size of Cohen’s d would be 0.255, 95% CI [0.076,0.434]. This effect size is substantially smaller compared to what has been found in another less intensive school-based intervention aiming to increase pupils’ FL [57]. This suggests that even though the intended recruitment level is not achieved, or a high drop-out rate becomes prevalent, the study will be sufficiently powered.

#### 2.4.5 Statistical analyses.

Linear mixed models will be applied to assess the intervention effects on FL, CCL, and SM [58]. Two-tailed tests with p-values below 0.05 will be considered statistically significant.

The analyses will account for the pupils’ nesting in their school classes by introducing school class as a random effect in the models. Intervention effects will be estimated through the inclusion of a group variable (intervention or control) and by adjusting for the outcome measure at baseline as well as confounders. Significantly better developments in these measures in the intervention group compared to the control group when adjusting for baseline level and confounders will be interpreted as a positive effect of the GtB program. Due to the lack of randomization, the analyses will be adjusted for known confounders such as gender, and SES. The analysis on the effect of GtB on FL will be further adjusted for participation in food and cooking classes during fourth grade or first semester of fifth grade. The analyses on the effect of GtB on FL and CCL will also be adjusted for age. Lastly, ICCs will be calculated by running the linear mixed models without the covariates to assess potential variation among school classes as fractions of the total variance. All analyses will be conducted using RStudio (version 1.4.1106; RStudio, Inc.) and IBM SPSS Statistics (version 29.0.1.0; IBM Corp.).

The models are expressed as follows:

$$\begin{array}{l} \text{Effect of GtB on FL:Endline FL }(\text{Y})=({\text{β}}_{0}+{\text{b}}_{\text{class}})+{\text{β}}_{1}\text{ FL baseline}+{\text{β}}_{2}*\text{int\_con}+{\text{β}}_{3}*\text{gender}+\\ {\text{β}}_{4}*\text{SES}+{\text{β}}_{5}*\text{age}+{\text{β}}_{6}\text{ food\_cooking\_class}+\text{ε} \end{array}$$

$$\begin{array}{l} \text{Effect of GtB on CCL:Endline CCL }(\text{Y})=({\text{β}}_{0}+{\text{b}}_{\text{class}})+{\text{β}}_{1}\text{ CCL baseline}+{\text{β}}_{2}*\text{int\_con}+\\ {\text{β}}_{3}*\text{gender}+{\text{β}}_{4}*\text{SES}+{\text{β}}_{5}*\text{age}+\text{ε} \end{array}$$

$$\begin{array}{l} \text{Effect of GtB on SM:Endline SM }(\text{Y})=({\text{β}}_{0}+{\text{b}}_{\text{class}})+{\text{β}}_{1}\text{ SM baseline}+{\text{β}}_{2}*\text{int\_con}+\\ {\text{β}}_{3}*\text{gender}+{\text{β}}_{4}*\text{SES}+\text{ε} \end{array}$$

Explanation for model concept for effects on FL, CCL and SM:

Y = The dependent variable (outcome) being analyzed, in terms of a score after the intervention.β_0_ +b_class_ = The intercept of the model.β_0_ represents the fixed intercept, which is the expected value of Y when all predictor variables are set to zero.B _class_ is the random intercept for class, which accounts for potential similarities among pupils within the same class.β_1_ * baseline = The effect of baseline for the outcome.This controls for pupils’ baseline levels before the intervention.β_1_ represents how changes in baseline influence Y.β_2_* int_con = The effect of *int_con*, represented by an intervention-control group variable.β_2_ captures the difference in Y (the outcome variable) between intervention and control groups.β_3_ * gender = The effect of gender.Gender is coded as a categorical variable (0 = boy, 1 = girl, 2 = other). β_3_ represents the difference in Y (outcome) between genders (boy, girl or other).β_4_* SES = The effect of socio-economic status (SES).β_4_ takes into account how changes in SES impact Y (the outcome).β_5_*age = The effect of age.β_5_ takes into account how changes in age impact Y (the outcome).β_6 *_ food_cooking_class = The effect of food and cooking class.β_6_ takes into account how changes in food and cooking class impact Y (only for FL).ε = The residual error term, capturing unexplained variation in Y.

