**Setting:**

Six GtB school garden locations across Region Zealand and Region of Southern Denmark.

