## 2. Materials and methods

The FoodACT study will comprise a multimethod, quasi-experimental inquiry into the existing school garden program GtB. RCTs are widely used in educational research to reduce bias in estimating the effects of the intervention [46]. RCT studies have previously shown health effects of school garden interventions [11]. However, when applied to school settings, RCTs necessitate a somewhat artificial (“unnatural”) intervention from outside the school system itself, which does not reflect how educational initiatives or programs are implemented, established, and scaled up in real life. In other words, RCT designs enable high internal validity regarding effects but often have low external pragmatic/ecological validity because the intervention investigated does not reflect real-life school practices well and often cannot be implemented long-term or scaled up in municipals and schools without significant alterations. The aim of the FoodAct study was to study the impacts of an already established school-garden program, namely the GtB program. This was chosen in order to ensure scalability and sustainable implementation of the intervention studied which is important for pragmatic validity or practical/political relevance of the study. The GtB program is implemented at the municipality level, which means that it is a political decision to financially prioritize whether the schools within the municipality get to participate in GtB or not. Randomizing which schools or classes would get to participate is thus not acceptable from a municipal perspective (in Denmark) making it impossible to recruit municipalities and hence schools to an RCT trial of this school garden program. We therefore chose a natural experiment approach [47–49] to evaluate the outcomes associated with participating in an already developed, established, and widely used school garden program in Denmark. Based on the practical nature of the GtB program, the study will be a non-randomized controlled natural experiment [44], drawing on various study designs through sub-studies (see Fig 3), which will be elaborated upon in the following sections.

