### 2.2 Recruitment and participants

The recruitment and enrollment of fourth grade pupils in the study was first initiated in September 2023 and ended in January 2024. Municipalities decide whether to offer the GtB program to schools within their district, which then sign up for the program on a yearly basis. All contact information for the schools will be provided by GtB. All contact information for the schools will be provided by GtB. School classes from public primary (non-private) schools that are signed up for the GtB program in 2024 but will not yet have started the program will be invited to participate in the intervention group via e-mail. Similarly, school classes who have not previously been and will not be enrolled in GtB in 2024 will be invited to participate in the control group via e-mail. The recruitment and inclusion of control classes will be based on similarity with the intervention schools regarding geographical proximity and average disposable income at the municipal level to enhance comparability between the intervention and control schools. First, a list will be comprised of municipalities that approximately match intervention municipalities on average disposable income (based on 2017 data from Statistics Denmark) [51] and are in the closest possible geographic proximity to the intervention municipality. For example, intervention schools located on the Danish Island of Funen will be matched with control schools in a different municipality on Funen but with a similar municipal average disposable income. Based on this list, public primary (non-private) schools within suitable control municipalities will be invited to participate, and an even distribution of school classes within the matched municipalities will be attempted. However, all schools indicating that they wish to participate will be enrolled in the study.

As part of the recruitment, teachers will be asked to provide all parents with written information about the study. Parents will subsequently be invited to provide electronic informed consent for their children’s participation. For SS2 and SS3, pupils will be asked to provide oral consent on the day of data collection. The recruitment process will be supported by general information available on the study project website [52]. By the end of data collection, all participating classes, including the control group, will receive a reimbursement equivalent to 200 EUR in recognition of their contribution.

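### SS1 models and minimum detectable effect cluster on class only, although exposure is set by municipality and school; any residual variance at those levels makes the standard error of the GtB effect too small

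*Protocol article*

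**What the plan says.** Section 2 of the protocol article places the exposure decision with local government: "The GtB program is implemented at the municipality level, which means that it is a political decision to financially prioritize". Section 2.2 adds a second step, in which schools in a participating municipality sign up year by year. It draws controls from a list of other municipalities that roughly match on average disposable income and lie close by. The abstract gives the setting as "Six GtB school garden locations across Region Zealand and Region of Southern Denmark".

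Section 2.4.5 accounts for clustering "by introducing school class as a random effect in the models". The FL, CCL and SM equations each contain one random intercept, for class, and no term for school, municipality, garden or matched area. A significant group coefficient is to be read as a positive effect of GtB.

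The power calculation in section 2.4.4 uses the same structure: "the clustered nature of data with pupils nested in classes was considered". It gives a minimum detectable effect size (MDES) of 0.255 for 25 classes per group. From this it argues that even if recruitment falls short or "a high drop-out rate becomes prevalent, the study will be sufficiently powered".

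**The concern.** As the design is described, every class in a municipality is in the same arm. Variation between municipalities therefore does not cancel within the comparison; it averages out only over the number of municipalities. The same holds for schools. A model with only a class intercept takes this variation to be class variation and averages it over up to 150 classes.

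The standard error of the group coefficient, β2, is then too small whenever some school or municipality variance remains after adjustment. That coefficient answers Hypothesis 1 for all three outcomes, so a chance difference between a few municipalities could be declared an effect of the program. The MDES has the same gap, since it counts 50 classes as independent units.

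This is not a detail left to an analysis plan: the article writes the model equations out in full.

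**Working it through.** **Inputs from section 2.4.4.** 25 classes per group (J = 50), n = 18 pupils per class, ICC 0.046, three covariates; "2-tailed level significance (0.05) were applied"; "conventional levels of statistical power (0.8"). The target of 75 classes per group (J = 150) is from section 2.2.

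**The stated figure reproduces.**

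SE = √[0.046/(0.25×50) + 0.954/(0.25×50×18)] = √(0.00368 + 0.00424) = 0.0890.

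With df = 50 − 3 − 2 = 45, the multiplier is 2.014 + 0.850 = 2.864, so MDES = 2.864 × 0.0890 = 0.255. The interval is 0.255 ± 2.014 × 0.0890, or 0.076 to 0.434. This matches the article, with covariate R² = 0. The arithmetic is right; it is a class-level calculation.

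**Adding the municipality level.** Let K be the total number of municipalities and ρ the municipality ICC, taken out of the 0.046:

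Var = 4[ρ/K + (0.046 − ρ)/J + 0.954/(18J)], with df = K − 2.

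Neither K nor ρ is in the article, so both are assumed. K = 12 to 18 means 6 to 9 per arm: six is the number of garden locations in the study, and section 2.1 puts gardens in nine municipalities nationwide. Municipalities are taken as equal in size.

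Example with J = 150, K = 12, ρ = 0.01:
- True SE = √{4[0.000833 + 0.000240 + 0.000353]} = 0.0755.
- Class-only SE = √{4[0.000307 + 0.000353]} = 0.0514.
- Ratio = 1.47.
- The class-only critical value of 1.976 acts as 1.976/1.47 = 1.34, giving a two-sided type I error of about 18%.

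**75 classes per arm** (class-only MDES 0.145). Each cell gives K = 12, then K = 18:

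| ρ | SE ratio | Type I error | MDES |
|---|---|---|---|
| 0 | 1.00, 1.00 | nominal | 0.160, 0.153 |
| 0.001 | 1.06, 1.04 | 6.1%, 5.7% | 0.169, 0.159 |
| 0.002 | 1.11, 1.07 | 7.5%, 6.5% | 0.177, 0.164 |
| 0.005 | 1.26, 1.17 | 11.6%, 9.1% | 0.201, 0.180 |
| 0.01 | 1.47, 1.32 | 17.9%, 13.4% | 0.235, 0.202 |
| 0.02 | 1.82, 1.58 | 27.8%, 21.0% | 0.291, 0.242 |

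A 20,000-run simulation over ρ = 0.005–0.02 gave 9.2–28.6%, in line with the closed form. With 30 municipalities the same ICC range still gives about 7–14%.

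**25 classes per arm** (stated MDES 0.255):

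| ρ | SE ratio | Type I error | MDES |
|---|---|---|---|
| 0 | 1.00, 1.00 | nominal | 0.277, 0.266 |
| 0.005 | 1.08, 1.04 | 6.1%, 5.4% | 0.298, 0.277 |
| 0.01 | 1.15, 1.09 | 8.0%, 6.4% | 0.318, 0.288 |
| 0.02 | 1.28, 1.17 | 11.6%, 8.4% | 0.354, 0.310 |

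The rows at ρ = 0 show that part of the rise comes only from fewer degrees of freedom. At ρ = 0.01 and K = 12, going from 25 to 75 classes per arm raises the ratio from 1.15 to 1.47. More classes in the same municipalities make the understatement worse.

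**School level alone.** With two classes per school (assumed), 75 classes per arm and a school ICC of 0.01–0.046, type I error is about 6–10% and MDES 0.153–0.177.

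**The case against.** **The size rests on assumed inputs.** This stands. The upper end, 28%, needs 0.02 of the 0.046, or 43% of the between-class variance, to lie between municipalities. What matters is the variance left after matching on income and proximity and after adjusting for baseline, gender and SES, and that may be small. The number of municipalities is not stated either: six counts garden locations, and a class may use a garden near its own municipality.

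**A reader might infer that the study is underpowered.** The article does not support that. It calls 0.255 substantially smaller than an effect seen in another study but gives no figure for that effect, so nobody can tell from the article whether 0.28–0.35 is also below it. At 75 classes per arm, most of the corrected range is under 0.255. The stated MDES also takes no credit for baseline adjustment, which every SS1 model includes. If R² = 0.3 at all levels (assumed), the worst 75-class case is 0.291 × √0.7 = 0.244. If R² = 0.5, the worst 25-class case is 0.354 × √0.5 = 0.250.

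**A reader might also infer that the matching is loosened** by "However, all schools indicating that they wish to participate will be enrolled in the study". In context, that sentence follows the attempt at an even spread of classes over matched municipalities and most naturally qualifies that attempt. It does not say that schools from unmatched municipalities are admitted.

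**Shared garden facilitators do not support the type I figures.** They exist only in the intervention arm, and with no program effect they add no variance.

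None of this removes the mismatch between the level of allocation and the level of clustering. The discussion in section 3 concedes the lack of randomization but does not deal with this variance.

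**Conclusion.** The concern holds as a mismatch. Exposure is fixed by municipality and then by school, while the written models and the MDES stop at class. Any residual variance above class makes the standard error of β2 too small.

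The direction of the error is certain if such variance exists; the size is not known. On the stated assumptions (12 to 18 municipalities, 75 classes per arm), the effect on type I error runs from none at zero municipality variance, through a slight excess at an ICC of 0.001–0.002, to a serious one at 0.005–0.02, where the true standard error is 1.17 to 1.82 times the reported one. The statement on power is unsupported at the level of allocation. It is not shown to be false.

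**What to change.** In section 2.4.5, add random intercepts for school and for municipality (or garden and control area) above class, with Kenward-Roger or Satterthwaite degrees of freedom for the group term. If the municipality variance estimate is singular, use cluster-robust standard errors at municipality level with a few-clusters correction (CR2).

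In section 2.4.4, restate the MDES over a stated range of school and municipality ICCs and municipality counts, and state the R² credited to baseline adjustment, if any. Qualify the sentence on sufficient power accordingly.

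The cost is wording and a few model terms, since school and municipality are known from recruitment. The price is wider intervals and a less favourable stated MDES.
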